**Methods/Design:**

In a two-armed randomized multicenter interventional study, patients after sepsis (n = 290) will be assessed at 6, 12 and 24 months. Patients are eligible if severe sepsis or septic shock (ICD-10), at least two criteria of systemic inflammatory response syndrome (SIRS), at least one organ dysfunction and sufficient cognitive capacity are present. The intervention comprises 1) discharge management, 2) training of general practitioners and patients in evidence-based care for sepsis sequelae and 3) telephone monitoring of patients. At six months, we expect an improved primary outcome (health-related quality of life/SF-36) and improved secondary outcomes such as costs, mortality, clinical-, psycho-social- and process-of-care measures in the intervention group compared to the control group.

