### Outcome measures

Measurements take place from 3 months before hospitalization (**T-1**, retrospectively) until 1, 6, 12 and 24 months after discharge from the ICU (**T1-4**).

Primary outcome is the health-related quality of life assessed by the Short Form 36 Health Questionnaire (SF-36), a multidimensional construction of physical, mental, social and behavior-related components of well-being and operational capability, validated also for German primary care [35].

Secondary outcomes focus on the most relevant sepsis sequelae, including the assessment of physical activity, level of pain, and cognitive deficits or neuropathic symptoms by established questionnaires, all of which are patient-reported outcomes.

Furthermore, for GP compliance review, treatment and cost-effectiveness analysis, patient rehospitalizations, medication, care needs, mortality, physical therapy and instrumental diagnostic procedures are documented by the primary care provider. GPs are asked to provide details of their practice characteristics.

For clinical analysis, diagnoses and ICU procedures are extracted from the ICU documentation system.

For detailed variable/outcome parameter descriptions see Table 1 and Additional file 4.

**Table 1 T1:** List of variables/outcome parameters

**Variables**	**Time of measurement**	**Instrument used (number of items)**
Intensive care unit (ICU)		
Documentation		
ICU stay	T_1_	Days
Mechanical ventilation	T_1_	Days
Kidney replacement therapy	T_1_	Days
Diagnoses at ICU discharge	T_1_	ICD-10
Focus of infection	T_1_	schematized (13)
Microbiological analysis	T_1_	pathogen cluster (8)
Use of sedatives, steroids	T_1_	schematized (4)
Patient reported		
Educational status	T_1_	schematized (2)
Socio-economic status	T_-1 to 4_	schematized (8)
Outcome measure (patient ratings)		
Health-related quality of life	T_-1 to 4_	Short Form 36 Health Survey (SF-36) (36) [35]
Depressive symptoms	T_1 to 4_	Major Depression Inventory (MDI) (12) [36]
Post-traumatic symptoms	T_1 to 4_	Post-Traumatic Stress Syndrome 10-Questions Inventory (PTSS-10) (10) [37]
Motoric function	T_2 to 4_	Short Musculoskeletal Function (XSMFA-D) (16) [38]
Impairment of swallowing, hearing, smelling	T-_1 to 4_	4-stepped Likert scale (4)
Chronic pain	T_1 to 4_	Graded Chronic Pain scale (GCPS) (7) [39]
Neuropathic symptoms	T_1 to 4_	Neuropathic Symptom Score (NSS) (6) [40]
Nutritional status	T-_1 to 4_	Malnutrition Universal Screening Tool (MUST) (4) [41]

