Cognitive status	T_1 to 4_	Telephone Interview of Cognitive Status (TICS-M) (21) [42,43]
Sleep	T_2 to 4_	Regensburg Insomnia Scale (RIS) (15) [44]
Medication addiction	T_2 to 4_	Short form for medication use (KFM) (12) [45]
Patient assessment of care	T_-1, 2 to 4_	Patient Assessment of Care for Chronic Conditions (PACIC) (20) [46,47]
Compliance/adherence	T_-1,2 to 4_	Modified Morisky questionnaire (4) [48]
Activities of daily life	T_2 to 4_	(Instrumental) Activities of daily life (ADL/IADL) (11)
General practitioner (GP) documentation		
Mortality	T_2 to 4_	
Current diagnoses	T_-1,2 to 4_	ICD-10
GP consultation	T_2 to 4_	Number
Stay in hospital	T_2 to 4_	Days
Inability to work	T_2 to 3_	Days
Medication	T_-1, 2 to 4_	agent, dosage
Stay in rehabilitation clinic	T_1 to 4_	Days
Remedies and therapeutic aids	T_2 to 4_	schematized (1)
Nursing level	T_2 to 4_	schematized (2)
Contacts to specialists, diagnostic procedures	T_1 to 4_	schematized (7)

To gain insight into processes, barriers and mechanisms of the intervention, qualitative interviews with patients and GPs are performed on a subsample. In this context, the roles of patients’ relatives are also to be evaluated.

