### Data analysis

Randomization process will be proofed using binary logistic regression. The dependent variable logarithmic odds ratio of patient is in the intervention versus control group. As predictors, we use potential confounders (for example, socio-demographic or clinical variables). Primary outcome will be analyzed based on a two-sided t-test. Secondary endpoints will be analyzed depending on scale level, using descriptive or hypothesis generating test procedures. For evaluation of average treatment effects, we will analyze the outcome variables with a generalized analysis of covariance (g-ANCOVA) and control for potential confounders. Based on these results, we are able to adjust means, which are comparable with outcome means of a perfect randomized and balanced design [49,50].

Furthermore, mortality is taken into account. Using survival analysis models, we are able to examine the relationship between mortality and treatment. In this way, we also try to identify mortality risk factors.

Finally, we plan cost-effectiveness analyses. Therefore, we sum up the costs of micro interventions and compare the averages of treatment and control group using g-ANCOVA (see above).

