### Description of risks

Showing 6- month mortality of more than 30% [25], severe sepsis ranks among critical long-term conditions. Serious risks or undesired effects of completing questionnaires have not been reported by clinical expertise of the scientific experts in the advisory board of the study (see Additional file 1). There are no specific risks related to the intervention. Thus, there are no rules for stopping the intervention.

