### Strengths/conclusion

To our knowledge, SMOOTH is the first study evaluating the effects of a primary care-based intervention for patients after a critical illness, that is sepsis [16]. Using established primary care structures, SMOOTH may provide a cost-effective addition to sepsis aftercare. Furthermore, considering the long-term impact of sepsis sequelae, 24-month follow-up data will be provided, which are rarely published and allow analysis of intervention sustainability. As a further innovative element, an external medical consultant in primary care (the liaison physician) might help to support quality of care in primary care settings - strengthening the GP as a reliable clinical partner for patients after critical illness.

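### The planned cost-effectiveness analysis is defined as a comparison of mean costs, with no effect measure and no link to survival, so taken alone it cannot show whether the program is cost-effective

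*Protocol article*

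**What the plan says.** The last paragraph of Data analysis opens with "Finally, we plan cost-effectiveness analyses". The next sentence gives the method: "we sum up the costs of micro interventions and compare the averages of treatment and control group using g-ANCOVA". The same section applies g-ANCOVA to the outcome variables and examines mortality in separate survival models.

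The Abstract expects "improved secondary outcomes such as costs, mortality, clinical-, psycho-social- and process-of-care measures", so costs and mortality stand there as separate secondary outcomes. Outcome measures lists what the GP documents "for GP compliance review, treatment and cost-effectiveness analysis, patient rehospitalizations, medication, care needs, mortality, physical therapy and instrumental diagnostic procedures". Table 1 has the SF-36 at every time point from T-1 to T4 and mortality from T2 to T4. Strengths/conclusion hopes that "SMOOTH may provide a cost-effective addition to sepsis aftercare".

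The article does not state the horizon over which costs are summed, the perspective, or whether patients who die stay in the cost average.

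**The concern.** A cost-effectiveness analysis sets a difference in cost against a difference in effect. The method described contains only the first. This is more than a detail left out of a condensed article: the text names one analysis and specifies another.

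Two things are at stake. First, the program adds discharge management, training and telephone monitoring, so costing more while doing some good is a plausible result. A difference in mean costs cannot then say whether the benefit justifies the expense. Second, patients who die stop generating costs. Where deaths are common, a cost average that ignores survival counts added survival only as expense, or, if dying is itself expensive, counts it as a saving. Either way the cost difference mixes the intensity of care with time alive.

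**Working it through.** The plan gives no figure for this point, so there is none to reproduce. The check has two parts.

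**1. What the cost comparison can and cannot decide**

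Let ΔC be the difference in mean cost and ΔE the difference in mean effect (intervention minus control), and λ the value placed on one unit of effect. Net benefit is λ·ΔE − ΔC.

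- ΔC < 0 and ΔE > 0: the program dominates. Separate results for cost and effect, read side by side, would show this.
- ΔC > 0 and ΔE < 0: the program is dominated. Again, separate results would show it.
- ΔC and ΔE of the same sign: the answer depends on λ and on the size of ΔE relative to ΔC.

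The stated method estimates ΔC alone, so by itself it settles none of these cases. In the third, separate tests of cost and effect do not settle it either. The variance of net benefit, λ²·Var(ΔE) + Var(ΔC) − 2λ·Cov(ΔE, ΔC), needs the covariance of cost and effect, which separate analyses do not provide.

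**2. How far deaths could move a cost-only comparison**

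Input from the article: "Showing 6- month mortality of more than 30% [25], severe sepsis ranks among critical long-term conditions" (Description of risks). Sample size also plans with 30% mortality.

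Assumptions that are not in the documents:
- 20% mortality in the better arm;
- the same monthly cost c while alive in both arms;
- no cost after death, and deceased patients kept in the average;
- a terminal cost L for each death.

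With deaths uniform over a horizon of T months and mortality p over that horizon, mean cost per randomized patient is

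c·[T(1 − p) + p·T/2] + p·L.

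Dividing by c·T and writing ℓ = L/(c·T) gives m(p) = 1 − p/2 + p·ℓ.

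| Terminal cost ℓ | m(0.30) | m(0.20) | Lower-mortality arm relative to the other |
|---|---|---|---|
| 0 | 0.850 | 0.900 | 0.900/0.850 = 1.059, 5.9% higher |
| 1/4 | 0.925 | 0.950 | 0.950/0.925 = 1.027, 2.7% higher |
| 1/2 | 1.000 | 1.000 | no difference |
| 1 | 1.150 | 1.100 | 1.100/1.150 = 0.957, 4.3% lower |

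The break-even terminal cost is T/2 months of ordinary cost: 3 months for T = 6 and 12 months for T = 24.

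If instead every death occurs at the start and costs nothing, mean cost is c·T·(1 − p). The ratio is 0.80/0.70 = 1.143, or 14.3% higher. That is the upper bound for this pair of mortalities under equal monthly cost.

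If mortality is equal in the two arms, the difference is zero in every row.

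**The case against.** The strongest reply is that health economics gets two sentences in a journal article, and that ratios, utility indices and bootstrap details belong in a fuller plan that is not shown. This stands for the details: their absence is no defect. It does not remove the mismatch, because the sentence that sets out the method specifies a cost comparison. A fuller plan may add an effect measure, but the published text would still need correcting.

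A second reply is that mortality is named among the data collected for this purpose, and that g-ANCOVA also yields adjusted effects on the outcomes, so cost and effect could be read together. This stands for dominance only, and without joint uncertainty. Also, the hope in Strengths/conclusion is tentatively worded, and costs are a secondary outcome. This limits the weight of the point.

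Three stronger readings are tempting, and the documents do not support them.

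- *The analysis makes the arm with more deaths look cheaper.* This needs a mortality difference, deceased patients kept in the average, and costs around death below what survival would have cost. The article fixes none of these, and the table shows the sign reversing.
- *The distortion is 14%.* That is the extreme case of immediate, costless deaths, under an assumed 10-point mortality difference that the article nowhere predicts.
- *The cost total leaves out second-year work loss.* Table 1 records "Inability to work" only at T2 to T3, while hospital stay, medication and GP consultations run to T4. But the article states neither a 24-month cost total nor that work loss enters the costs, and work loss is not in the list of data named for the cost-effectiveness analysis. The schedule contradicts nothing; it only limits what a work-loss analysis could cover.

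**Conclusion.** The point holds for the method as stated. The analysis called cost-effectiveness is a comparison of mean costs. Taken alone it cannot show whether the program is cost-effective, and it leaves the question open in the plausible case of higher cost with greater benefit. This part rests on the text alone.

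The effect of deaths is a risk and not an established bias. For 30% versus 20% mortality and equal monthly cost, the lower-mortality arm's mean cost is about 6% higher with uniform deaths and no terminal cost, and at most 14% higher with immediate deaths. The difference vanishes at a terminal cost of half the full-horizon cost and reverses above that (uniform deaths). These figures depend on the assumed mortality difference and on how deceased patients are handled, which the article does not state. The article's figure of more than 30% describes severe sepsis; mortality among patients enrolled after ICU discharge may differ.

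The primary comparison is untouched. The plan should be changed because a stated conclusion depends on this analysis and the repair is cheap.

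**What to change.** Either of two changes resolves the point.

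1. **Keep the name and add the effect.** Declare an effect measure, a horizon and a perspective. One option that uses data already collected is QALYs from a preference-based index derived from the SF-36, with death counted as zero from the date of death. Estimate incremental cost and incremental effect jointly in all randomized patients, and state that deceased patients stay in both averages. Report net benefit or an incremental ratio, with uncertainty from a bootstrap that resamples each patient's cost and effect together.
2. **Keep the method and change the name.** Call it a cost comparison, state how deaths are handled, and draw no cost-effectiveness conclusion from it.

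If work loss is to count as a cost, limit that analysis to 12 months, since Table 1 does not record it at T4.

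The first change costs extra analysis work only, because the SF-36, mortality and resource use are already in the data collection. The second costs a change of wording.

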### Description of risks

Showing 6- month mortality of more than 30% [25], severe sepsis ranks among critical long-term conditions. Serious risks or undesired effects of completing questionnaires have not been reported by clinical expertise of the scientific experts in the advisory board of the study (see Additional file 1). There are no specific risks related to the intervention. Thus, there are no rules for stopping the intervention.

### Ethical principles

The study is planned and conducted in accordance with medical professional codex and the Helsinki Declaration of 1996 as well as the Federal Data Protection Act (BDSG).

Patients participate in the study voluntarily and give written informed consent. Patients are informed that they can cancel their participation at any time without disclosing reasons for their cancellation and without negative consequences for their future medical care. The study protocol was approved by the institutional review board of the University of Jena, 26 January 2011 (No.3001/111).

### Data security

The patient names and other confidential information are secured by the medical confidentiality rules and are treated according to Federal Data Protection Act (BDSG).

All study-related data and documents are stored on a protected central server at Jena University Hospital. Only members of the study team have access to the study files.

Intermediate and final reports are stored in the office of the Institute of General Practice and Family Medicine at the Jena University Hospital.

## Discussion

### Limitations

Contacting control patients via phone calls for data collection may create a small intervention (Hawthorne) effect in the control group. Therefore, the intervention effect is likely to be underestimated. This might be acceptable because we would not overuse any effect of the trial.

In addition, contamination by information flow between the intervention and control group cannot be excluded. However, this risk seems to be minimized by the allocation of one GP to one patient of either intervention or control group. Most GPs in Germany practice alone.

### Strengths/conclusion

To our knowledge, SMOOTH is the first study evaluating the effects of a primary care-based intervention for patients after a critical illness, that is sepsis [16]. Using established primary care structures, SMOOTH may provide a cost-effective addition to sepsis aftercare. Furthermore, considering the long-term impact of sepsis sequelae, 24-month follow-up data will be provided, which are rarely published and allow analysis of intervention sustainability. As a further innovative element, an external medical consultant in primary care (the liaison physician) might help to support quality of care in primary care settings - strengthening the GP as a reliable clinical partner for patients after critical illness.

## Trial status

The first patient was included on 28 February 2011. Patient recruitment is ongoing but not completed.

## Abbreviations

CSCC: Center of Sepsis Control and Care; g-ANCOVA: generalized analysis of covariance; GCPS: graded chronic pain scale; GP: general practitioner; GSS: German Sepsis Society; I/ADL: instrumental activities of daily life; ICD-10: international statistical classification of diseases and related health problems; ICU: intensive care unit); KFM: short form for medication use; MDI: major depression inventory; MUST: malnutrition universal screening tool; NSS: neuropathic symptom score; ODSS: modified overall disability sum score; PACIC: patient assessment of care for chronic conditions; PHQ-9: patient health questionnaire; PTSD: post-traumatic stress disorder; PTSS-10: post-traumatic stress syndrome 10-questions inventory; RIS: Regensburg insomnia scale; SF-36: short form 36 health survey; SIRS: systemic inflammatory response syndrome; SMOOTH: Sepsis Survivors Monitoring and Coordination in Outpatient Health care; STIFT: Thuringian Foundation for Technology, Innovation and Research; TICS-M: modified telephone interview for cognitive status; XSMFA-D: short musculoskeletal function.
